### Measures/outcomes for feasibility criteria and other objectives

The primary outcome of this trial is to understand the feasibility and acceptability of the SCAPE-U intervention. We have developed a set of quantitative and qualitative measures to do this as guided by recommendations from pilot study reporting [49]. These measures will determine what components of the SCAPE-U intervention will be included, excluded, or modified in the future full trial. The following quantitative criteria have been set to determine if this feasibility trial can be scaled up for a fully powered trial.Recruitment: at least 2 primary care workers were recruited in the study from each of the 36 health facilities selected.Retention: 50% of SCAPE-U facilitators retained by the end of PhotoVoice training, 60% of primary care workers, 60% of community health workers retained in post until the end of the 8 months follow-up period, and 50% of service users and families retained by the end of 5 session home visits.Contamination: less than 20% of cross-arm movement of primary care workers, community health workers, service users, and their families during the 8-month follow-up period.Cluster comparison: measuring baseline characteristics of recruited primary care and community health workers across both arms. We will collect information on primary care workers and community health workers’ education qualifications, gender, prior mental health training, age, and years of experience and determine balance between arms.Data collection procedure: less than 20% of missingness in collected data.Safety: fewer than 20% of adverse events among recruited SCAPE-U facilitators and service users.

Our qualitative criteria for this feasibility study are presented in Table 3.

**Table 3 Tab3:** Assessment of feasibility and acceptability of the intervention and trial procedures

Domains	Research questions	Methods
Feasibility and acceptability of SCAPE-U intervention	Do psychiatrist/psychiatric clinical officer, primary care workers, and mental health service users find it feasible and acceptable for PhotoVoice trained people with lived experience to participate as co-facilitators in training and supervision?	● Qualitative interviews with psychiatrist/psychiatric clinical officer, primary care workers, SCAPE-U facilitators, and research staff ● Process notes from trainings and supervision sessions
Fidelity and contagion of intervention	Can fidelity be feasibly and reliably assessed using a fidelity checklist? What degree of fidelity to SCAPE-U is achievable? Can contamination be captured through fidelity and other assessments?	● Qualitative interviews with psychiatrist/psychiatric clinical officer trainers, primary care trainees, SCAPE-U facilitators, and research staff ● Process notes and fidelity checklist from trainings and supervision sessions ● Logs of health workers and service users’ movement across arms
Ethics and safety of trial	Does the research pose harm to primary care workers, service users, or SCAPE-U facilitators, and are these harms adequately prevented, documented, and addressed?	● Qualitative interviews ● Service Users Collaboration Checklist ● Process evaluation notes ● Monitoring of adverse events

*Qualitative data* will be collected from PWLP, primary care and community health workers, service users, and their families, mental health specialists involved in training and research staff involved in data collection through key informant interviews (KIIs) and focus group discussions (FGD). We will conduct KIIs with 75% of the PWLP recruited to be SCAPE-U facilitators and who have completed PhotoVoice training and co-facilitated health workers training and home visits during two timepoints—after the health workers training and after home visits. For those who are just part of the PhotoVoice training, we will conduct an FGD talking about their experiences with PhotoVoice. For PCWs and VHTs, we will conduct KIIs with 15% of the total trained population. Selection will be based on gender, performance based on supervision notes, the number of mental health cases attended, and the level of health facility. We will interview them at 3 months post-training, i.e., during the first supervision. Twenty percent of the service users and their families receiving home visits will be interviewed after the completion of all five sessions. Finally, during the study’s end phase, we will interview all the trainers in both arms and research assistants involved in SCAPE-U data collection.

KIIs and FGDs will be conducted either in Luganda or English based on the participant’s preference and will be audio recorded. KIIs and FGDs will be held in either health facilities, YBU office, service user’s home, or anyplace deemed safe and confidential by both the interviewer and interviewee and will be conducted by YBU staff trained and with prior experience in qualitative data collection. All participants will be provided with information about the purpose of the KII/FGD and have written informed consent taken by the researcher.

*Quantitative data* will be collected to address objectives 3 and 6 (Table 1) of this feasibility trial and are related to quantitative outcomes listed in Table 4. Service user symptom severity will be assessed using the Positive and Negative Symptoms of Schizophrenia (PANSS) scale [50]. This tool measures the severity of positive and negative symptoms, with higher scores equating to greater symptom severity and has been widely used in psychosis research trials. Additional outcomes for the service users include quality of life measured using the World Health Organisation Quality of Life Brief Version (WHOQOL-BREF) [51] and European Quality of Life Five Dimension questionnaire (EQ5D-5L) [52], stigma measured through the Discrimination and Stigma Scale short version (DISCUS)[53], social inclusion measured through the Social Inclusion Scale (SIS) [54], and the number of hospitalization episodes coming from the service users’ self-reporting (see Table 4). A separate costing outcome will be included for the training of service users and primary care workers and health system context regarding cost for receiving and delivering care measured through the Client Service Receipt Inventory (CSRI) [55]. Impact on family caregivers will be measured through the Family Interview Schedule—Impact on Caregivers (FIS-IC) [56].

**Table 4 Tab4:** Quantitative outcome measures

Outcomes	Instrument or data collection strategy	Type of data	Respondent or source	Assessment period
PWLP recruited to become SCAPE-U facilitator				
Quality of Life	World Health Organization Quality of Life-Brief version (WHOQOL-BREF)	Self-report scale	PWLP as SCAPE- U facilitators	Enrolment, baseline,
Unintended consequences of participation in SCAPEU	Service Users Collaboration Checklist (SUCC)	Self-report scale guided with probing questions	PWLP as SCAPE- U facilitators	Mid and end point of PhotoVoice training, end of health workers training and PhotoVoice
Symptoms of psychosis	Positive and Negative Symptoms of Schizophrenia (PANSS) scale	Adapted scale for self-report	PWLP as SCAPE- U facilitators	
Service users with psychosis diagnosed by primary care workers				
Symptoms of psychosis	Positive and Negative Symptoms of Schizophrenia (PANSS) scale	Adapted scale for self-report (or report by a family member)	Service users or family members	Baseline, 4 and 8 months follow-up
Quality of life	World Health Organization Quality of Life-Brief version (WHOQOL-BREF)	Self-report scale	Service users	Baseline, 4 and 8 months follow-up
Quality of life (for health economics analyses)	EuroQoL 5-Dimension 5-Level (EQ-5D-5L)	Self-report scale	Service users	Baseline, 4 and 8 months follow-up
Stigma experienced by persons living with mental illness	Discrimination and Stigma Scale-Brief version (DISCUS)	Self-report scale	Service users	Baseline, 4 and 8 months follow-up
Social inclusion	Social Inclusion Scale (SIS)	Self-report scale	Service users	Baseline, 4 and 8 months follow-up
Hospitalization	# days hospitalized during study period	Self-report, family report, and/or hospital records	Service users or family members	4 and 8 months follow-up
Costs of services received	Client Service Receipt Inventory (CSRI)(54)	Self-report and/or family report	Service users or family members	4 and 8 months follow-up
Family members and caregivers of service users				
Impact on family members	Family Interview Schedule—Impact on Caregivers (FIS-IC) (56)	Family report	Main caregiver	Baseline, 4 and 8 months follow-up
Community health workers				
Attitudes towards people with psychosis	Social Distance Scale (SDS)	Self-report scale	Community health worker	Pre- and post-training
Accuracy of psychosis detection	Community health worker referral tool	Percent of community health worker referred patients who meet SCID criteria	Community health worker	Post training
# of individuals referred	Community health worker referral tool	Numbers	Community health worker	Throughout study
# of individuals referred by CHWs who receive a diagnosis of psychosis from PCP	Health facility records	Numbers	Research assistant reviewing clinical records	Throughout study
Primary care workers				
Outcomes	Instrument or data collection strategy	Type of data	Respondent or source	Assessment period
Attitudes towards people with psychosis	Social Distance Scale (SDS)	Self-report scale	Primary care workers	Pre- and post-training, and at final supervision session
Knowledge of psychosis diagnosis and treatment	mhGAP Knowledge	Self-report knowledge test	Primary care workers	Pre- and post-training, and at final supervision session
Clinical diagnosis skills in structured role plays	ENACT	Structured observational rating scale	Trained raters	Pre- and post-training, and at final supervision session
# of individuals diagnosed with psychosis	Health facility records	Medical records	Research assistant reviewing clinical records	Pre- and post-training, and at final supervision session
Fidelity of treatment to mhGAP guidelines	Fidelity Checklist	Observer completed fidelity checklist	Observations	Pre- and post-training, and at final supervision session
Accuracy of diagnosis (confirmatory diagnosis with SCID by PCO)	DSM-V psychosis module (SCID)	Structured clinical interview	Psychiatric clinical officer	Pre- and post-training, and at final supervision session

For primary care workers, the outcomes include attitudes measured through the Social Distance Scale (SDS) [57], knowledge measured through the mhGAP Knowledge assessment [58, 59], clinical competency measured through ENACT [60], fidelity of treatment measured through the fidelity checklist, and number of diagnosis data coming from health facility records. To determine diagnostic accuracy, a psychiatric clinical officer will use the SCID [61] to determine the diagnosis of a subset of service users diagnosed by the primary care workers. The psychiatric clinical officer’s diagnosis will be taken as the gold standard and matched with the primary care workers’ diagnosis.

Community health worker outcomes will include attitudes towards people with mental health conditions measured through the Social Distance Scale (SDS) [57] and data on number of referrals to primary care, and accuracy of psychosis detection derived using health facility data.

Timelines for quantitative data collection are presented in Table 4. Data will be collected by research assistants at the training site, health facility, or at the participants’ home. Study data will be collected and managed on Android tablets using REDCap (Research Electronic Data Capture) electronic data capture tools hosted at Infectious Disease Institute, Uganda. REDCap is a secure, web-based software platform designed to support data capture for research studies, providing (1) an intuitive interface for validated data capture; (2) audit trails for tracking data manipulation and export procedures; (3) automated export procedures for seamless data downloads to common statistical packages; and (4) procedures for data integration and interoperability with external sources [62]. Participants will receive 10,000 Ugandan shillings (US$ 2.70) for each completed assessment to compensate for time and travel costs (Table 5).

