**2. Recruitment and retention**	Can we recruit, train, and retain enough PLWP to be SCAPE-U facilitators? Can we recruit and retain sufficient primary care workers, community health workers and service users and their caregivers for outcome assessment?	PLWP can be adequately recruited, trained, and retained for delivering the SCAPE-U intervention For primary care workers, community health workers and service users and their families, maximum recruitment might be required to address loss to follow-up and drop-out	Process output: number of SCAPE-U facilitator recruited, completed training, and retained. Target = 50% retention For primary care workers, community health workers: number in health posts, number completing the training, supervision and completing outcome measures. Target for both = 60% at 8 months follow-up For SU and families: 50% completing the 5 session home visits	SCAPE-U facilitators, primary care workers, community health workers, service users and their families, research staffs
**3. Acceptability and feasibility measures and data collection procedures**	Are the quantitative and qualitative assessment measures and collection procedure acceptable and feasible to administer with the stakeholders at planned intervals?	The selected measures will be acceptable and feasible for measuring the intended outputs of the study	Tool completion rate, time, missingness of data (target: fewer than 20%)	Primary care workers, community health workers, service users and families, research staff
**4. Randomization**	Is cRCT feasible to run the study and measure the intended outcomes—in terms of contamination, fidelity, and implementation strategy?	Cluster randomization is feasible to execute the study and measure intended outcomes	Baseline summary of two arms Demographic details of primary care workers, community health workers (age, gender, years of experience, qualifications, education) Record on participant’s arm crossover (target: less than 30%)	Primary care workers, community health workers, service users and families, research staff

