### Study participants

This study will involve six categories of study participants:(i)People with lived experience of psychosis trained as SCAPE-U facilitators—8 to 10 people with lived experience of psychosis who have previously received services from YouBelong Uganda [33, 35] will be recruited. The inclusion criteria are (1) diagnosis of a psychotic disorder confirmed by a mental health professional (psychiatric clinical officer or psychiatrist). (2) Capacity to provide informed consent. The main exclusion criterion is any health, functional, or cognitive impairment, assessed through mental state examination, that could jeopardize their full and safe participation in SCAPE-U activities. There are no inclusion/exclusion criteria relating to current engagement in treatment.(ii)Primary care workers—two primary care workers will be selected per health facility, with a target of 36 primary care workers per arm (72 total for the study). There are no exclusion criteria.(iii)Community health workers—we will select up to five community health workers from each health facility. This will equate to approximately 90 community health workers per arm and an estimated total of 180 community health workers for the study.(iv)Psychiatrists, psychiatric clinical officers,and psychiatric nurses—1 psychiatrist, 3 psychiatric clinical officers, and 2 psychiatric nurses who are involved in delivering training to primary care workers will be included.(v)Service users diagnosed with psychosis by primary care workers—the primary intended beneficiaries of study interventions are service users receiving treatment for psychosis at primary care facilities. The goal is to have 10 service users per cluster, 30 per arm, and 60 in total for the study. *Inclusion criteria*: (1) persons diagnosed with psychosis at a primary health care facility in Kampala/Wakiso District, following mhGAP training as part of the SCAPE-U trial; (2) ability of the service users to consent to study enrollment and procedures, or, if the service user does not have capacity to consent, a responsible surrogate can give consent; (3) persons eligible for outpatient management of psychosis. *Exclusion criteria*: (1) persons diagnosed with psychosis requiring inpatient management; and (2) persons for whom consent for participation in the study cannot be obtained.(vi)Family members of service users—at least one primary carer for study service users will be identified to collect outcome data from a family perspective (*n* = 30 per arm, 60 for the total study).

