### SCAPE-U facilitator training

The training will prepare selected people with lived experience of psychosis, and the YouBelong community recovery program, to participate in primary care and community health worker training and to conduct home visits; they will be trained in PhotoVoice and hereafter referred to as SCAPE-U facilitators. PhotoVoice is based on participatory methods where photography is a medium of storytelling and message delivery [41–43]. SCAPE-U facilitators will use PhotoVoice narratives to cofacilitate training of PHWs and CHWs, as well as provide psychosocial support during home visits. The training, which will be delivered in Luganda, will involve a 2-day residential, followed by eight weekly sessions. SCAPE-U facilitators will learn about using cameras and taking pictures, writing recovery stories, practicing storytelling using photographs, public speaking, advocacy, addressing stigma, and managing confidentiality and disclosure. PhotoVoice has successfully been used to reduce stigma among persons living with severe mental health conditions and to facilitate peer support and community reintegration in the USA [44, 45]. The approach has also been tested through a pilot study in Nepal where people with lived experience of depression, psychosis, and alcohol use disorder participated in mhGAP-IG trainings of primary care workers [46, 47]. Findings from this study suggested this approach to training improved diagnostic accuracy and decreased stigma amongst primary care workers [22]. Details of the PhotoVoice training are described elsewhere [43].

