### Home level

Service users receiving service from the health facilities in the control arm will not receive any additional service besides that provided from health facilities. For those receiving service from the intervention arm and diagnosed with psychosis, SCAPE-U facilitators will conduct five 1-h home visits to service users who have been diagnosed with psychosis by primary care workers and are currently receiving treatment. Primary caregivers to service users are expected to be present during these visits. Each session will consist of SCAPE-U facilitators sharing their lived experiences through a 10-min presentation of an aspect of their PhotoVoice story. Each session will be tailored to a psychosocial theme (medication adherence, conflict resolution, stigma, livelihood support, and dealing with challenging behaviors) [33, 35]. There will then be time for questions and discussion with the service users and their family (Table 2).

**Table 2 Tab2:** Overview of services and implementation by study arm and level of care

Care level	Standard services arm	SCAPE-U arm
Primary care	mhGAP-IG training conducted by a psychiatrist and/or psychiatric clinical officer for 5 days with a focus on psychosis diagnosis and treatment	mhGAP-IG training conducted by a psychiatrist or psychiatric clinical officer combined with a SCAPE-U facilitator (people with lived experience of psychosis) presenting recovery stories and other activities
Community	2-day training conducted by trained psychiatric clinical officer or psychiatric nurse on identification and referrals of people potentially experiencing psychosis	2-day training conducted by trained psychiatric clinical officer or psychiatric nurse, combined with SCAPE-U facilitator presenting recovery stories and other activities
Home	No services	5 fortnightly sessions of psychosocial support provided by SCAPE-U facilitators using PhotoVoice narratives based on themes in the YouBelongHOME intervention

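### Facilitator retention is judged before delivery begins, and service-user retention only on home visits in the intervention arm, so neither criterion answers Objective 2

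*Protocol article*

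**What the plan says.** The section on measures and outcomes for feasibility criteria lists the quantitative rules for deciding whether to go on to a fully powered trial. Those that bear on this point are:

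- **Facilitators:** "50% of SCAPE-U facilitators retained by the end of PhotoVoice training".
- **Service users and families:** "50% of service users and families retained by the end of 5 session home visits".
- **Primary care and community health workers:** 60% of each group still in post at 8 months.
- **Recruitment:** at least two primary care workers from each of the 36 facilities. No other recruitment number is listed.
- **Missing data:** "Data collection procedure: less than 20% of missingness in collected data".

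Table 1, Objective 2, asks: "Can we recruit and retain sufficient primary care workers, community health workers and service users and their caregivers for outcome assessment". Its hypothesis for facilitators is that they can be recruited, trained and kept on in order to deliver the intervention. Its facilitator entry reads "number of SCAPE-U facilitator recruited, completed training, and retained. Target = 50% retention", with no time point. Its service-user entry is 50% completing the five home-visit sessions.

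On the control arm, the Home level section says: "Service users receiving service from the health facilities in the control arm will not receive any additional service besides that provided from health facilities". Table 4 schedules most service-user and carer outcomes at baseline, 4 and 8 months. The Data analysis section compares change in PANSS from baseline to month 8 between arms.

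**The concern.** These criteria serve the primary outcome of the trial and decide whether a larger one follows. Two of them measure something other than what Objective 2 asks.

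The distinctive question here is whether people with lived experience of psychosis stay involved while they deliver training, supervision and home visits. The facilitator criterion closes before any of that starts.

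A definitive trial also needs to know how many service users and carers can be assessed at 8 months, and whether loss differs between arms. The service-user criterion records adherence to an intervention component in one arm. A favourable result on it would say nothing about control-arm follow-up or about later loss in either arm. People with no post-baseline assessment also drop out of the planned change analyses.

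**Working it through.** **The plan's own figure.** The only precision calculation is in the Sample size section: 80% of 60, Wilson 95% interval 68.2% to 88.6%. For 48/60 the Wilson formula gives 68.2% to 88.2%, so the upper limit is slightly off. That is a separate small matter. The figure concerns baseline completion, so the protocol gives no calculation for retention.

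**Facilitators.** Inputs: "8 to 10 people with lived experience of psychosis" (Study participants); training that "will involve a 2-day residential, followed by eight weekly sessions" (SCAPE-U facilitator training).

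- Threshold: 0.5 × 8 = 4, or 0.5 × 10 = 5.
- Wilson interval: centre (p + z²/2n)/(1 + z²/n), half-width z√[p(1−p)/n + z²/4n²]/(1 + z²/n), with z = 1.96.
- For 4/8: 50% ± 28.5 points, or 22% to 78%. For 5/10: 24% to 76%.
- Timing: after about 8 weeks of training. Co-facilitation, supervision and home visits all follow.

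**Service users.** Inputs: 30 per arm and 60 in total (Study participants); five fortnightly visits in the SCAPE-U arm and none in the control arm (Table 2).

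- Threshold: 0.5 × 30 = 15; Wilson interval for 15/30 is 33% to 67%.
- Duration: four gaps × 2 weeks = 8 weeks from first to last visit, or 5 × 2 = 10 weeks if each visit is given a full fortnight. At 4.345 weeks per month that is 1.8 to 2.3 months after visits begin.
- Users without any retention rule: 30 of 60, all in the control arm.

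**Does the service-user rule protect facilitator retention indirectly?** Partly. Fifteen users × 5 visits = 75 facilitator-led visits, out of 30 × 5 = 150 planned. Some facilitators must still be active, but no minimum number is implied.

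**Does the missingness rule cover service-user follow-up?** That depends on a denominator that the protocol does not give. Taking service users alone, with 60 enrolled and all loss at month 8:

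| Reading of the 20% limit | Planned assessments | Must be fewer than | Month-8 loss that still passes |
|---|---|---|---|
| Pooled over baseline, 4 and 8 months | 60 × 3 = 180 | 36 missing | just under 36/60 = 60% |
| Pooled over 4 and 8 months | 60 × 2 = 120 | 24 missing | just under 24/60 = 40% |
| Month 8 alone | 60 | 12 missing | just under 12/60 = 20% |
| Items within completed assessments | not applicable | not applicable | no bound |

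On the first reading, losing every control user at month 8 only gives 30/180 = 16.7% missing, which passes. Losing every control user after baseline gives 60/180 = 33%, which fails.

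**The case against.** The best defence has five parts.

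1. **Facilitators cannot all vanish.** A reader might infer that the trial could pass with every facilitator gone after training. The protocol does not support this: the service-user criterion requires about 75 facilitator-led visits. What stands is that no facilitator-retention threshold covers the delivery period.
2. **Table 1 separates training completion from retention.** It does, and its hypothesis points to delivery. But its 50% has no time point, and the criteria list, which does give one, sets it at the end of training. Interviews planned with facilitators after home visits inform the question without setting a threshold.
3. **Objective 3 may cover later loss.** Table 1 names service users and families, refers to planned intervals, and sets missingness below 20%. On some readings this would catch a collapse in control-arm follow-up. It would therefore be wrong to say that 8-month loss is certainly unbounded; the bound runs from just under 20% to none.
4. **The decision is not mechanical.** Qualitative criteria also count, the Discussion allows for modification or an internal pilot, and the monitoring board follows recruitment. All true. Still, these numerical criteria are the stated scale-up rules, so they should measure the stated objective.
5. **The service-user criterion could be read as a calendar point for both arms.** Table 1 counts completed sessions, which excludes controls. Even on the calendar reading, it would not reach month 8.

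A reader might also infer that 60% health-worker retention contradicts the 20% missingness limit. It does not. Being in post is about staffing and missingness is about data; two minimum requirements can both apply, and the stricter one binds.

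**Conclusion.** The concern holds for two criteria. Facilitator retention, at 4 of 8 or 5 of 10, is counted before delivery. Service-user and family retention, at 15 of 30, is counted in one arm when home visits end. No explicit retention criterion covers users or carers at 4 or 8 months in either arm, and the missingness rule cannot be relied on to fill the gap until its denominator is stated. As a secondary point, the only numerical recruitment criterion concerns primary care workers; none addresses the target of 10 service users per cluster, 60 in total.

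The health-worker retention criteria do run to 8 months and are not at issue.

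The conclusion rests on the recruitment targets being met and on visits keeping to the fortnightly schedule. The 8 to 10 weeks run from the first visit, whereas follow-up runs from enrolment; the gap between the two is not given, so the exact month of follow-up at which visits end is not known.

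**What to change.** Reword the criteria list and Table 1, Objectives 2 and 3:

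- **Facilitators:** count retention through the end of the home-visit period, with those recruited as denominator. Report end-of-training retention separately.
- **Service users and carers:** judge retention on completing the 8-month assessment, overall and by arm. Keep home-visit completion as a separate adherence criterion for the intervention arm.
- **Recruitment:** add a service-user criterion against the stated 10 per cluster and 60 in total.
- **Missingness:** count missed scheduled assessments, with all enrolled as denominator, by visit and arm. Report item-level missingness separately. Defining the rule as item-level only would remove the one existing criterion that might limit missed visits.

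The 8-month retention and missingness thresholds should be set together. With 30 per arm, 20% is 6, so a limit below 20% at month 8 allows at most 5 missing and needs at least 25 of 30 assessed. A 50% retention figure carried over unchanged would then never be the binding rule.

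The cost is small: the 8-month assessments are already scheduled, and facilitator activity can be counted as visits proceed. The downside is that the criteria become somewhat harder to meet.

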### Study design

The design is a cluster-randomized controlled feasibility trial comparing the standard implementation arm, where PCWs will be trained by mental health specialists, versus the intervention arm, where, in addition, PWLP will cofacilitate the PCWs training and provide home visits to the service users with psychosis.

The unit of randomization is a geographic cluster of primary care facilities. There are 36 primary care facilities in the two study districts. These will be divided into six geographic clusters based on a health subdistrict, each consisting of six primary care facilities. Three geographic clusters will be randomly allocated to the control arm and three to the SCAPE-U arm. We chose a cluster design because the interventions are delivered at a primary care facility and community level, meaning individual randomization is not possible. Having multiple health workers and primary care facilities in each cluster also ensures that we will not lose the entire cluster in the scenario that primary care workers or community health workers retire or are relocated by the government.

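### The 60% worker-retention target is defined in two ways that can give opposite verdicts, and the progression list carries the version that counts only staying in post

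*Protocol article*

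**What the plan says.** The section Measures/outcomes for feasibility criteria and other objectives introduces its list with "The following quantitative criteria have been set to determine if this feasibility trial can be scaled up for a fully powered trial". The retention entry for workers in that list is "60% of primary care workers, 60% of community health workers retained in post until the end of the 8 months follow-up period". It mentions no training, supervision or assessment for workers. In the same entry, retention of facilitators and of service users is tied to study activities: the PhotoVoice training and the home-visit sessions.

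Table 1, objective 2, asks "Can we recruit and retain sufficient primary care workers, community health workers and service users and their caregivers for outcome assessment". Its methods cell for the two worker groups reads "number in health posts, number completing the training, supervision and completing outcome measures. Target for both = 60% at 8 months follow-up".

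The progression list also has a data criterion: "Data collection procedure: less than 20% of missingness in collected data". It does not say which group, which time point or which denominator.

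Planned numbers are in Study participants: "two primary care workers will be selected per health facility, with a target of 36 primary care workers per arm (72 total for the study", and "approximately 90 community health workers per arm and an estimated total of 180 community health workers for the study". In Table 4, primary care workers are assessed before training, after training and at the final supervision session. Community health workers have an attitude scale before and after training. Their only data beyond training are referral and diagnosis counts gathered during the study.

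**The concern.** Holding a post and staying in the study are different events. A worker can remain employed at the facility, attend no supervision and give no final assessment, and still meet the wording of the progression list. Conversely, a post can be lost for reasons outside the trial: Study design allows for the case in which "primary care workers or community health workers retire or are relocated by the government".

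Table 1 frames the target as retention for outcome assessment, yet the list used to judge scale-up checks employment. If the two definitions part company, the protocol does not say which decides. At stake is whether the pilot can answer objective 2 for primary care workers, whose attitudes, knowledge and role-play competence all have their last measurement at the final supervision session.

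**Working it through.** **1. Denominators.** From Study design (36 facilities) and Study participants (two primary care workers and up to five community health workers per facility):
- primary care workers: 36 × 2 = 72, as the plan states;
- community health workers: 36 × 5 = 180, as the plan states.

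**2. Thresholds implied by 60%.**
- primary care workers: 0.60 × 72 = 43.2, so at least 44;
- community health workers: 0.60 × 180 = 108.

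**3. Test case.** Suppose all 72 primary care workers stay in post for 8 months and none completes supervision or the final assessment. This shows where the definitions diverge; it is not a forecast.

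| Definition | Count | Result against 60% |
|---|---|---|
| Progression list: in post | 72/72 = 100% | met |
| Table 1: supervision and outcome measures completed | 0/72 = 0% | not met |

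**4. Does the result depend on how Table 1 is read?** Table 1 does not say whether the 60% applies to each count separately or to all of them jointly. Applied separately, the in-post count is met but the supervision and outcome-measure counts are 0%. Applied jointly, the figure is 0/72. The target is missed either way. The two places agree only if the 60% in Table 1 is meant for the in-post count alone, and then the completion counts have no retention target.

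**5. Would the missing-data criterion catch it?** Count each planned assessment occasion once and suppose that only the 72 final primary care worker assessments are missing. The occasions below are taken from Study participants and Table 4, and counting them this way is an assumption:
- primary care workers 72 × 3 = 216;
- community health workers 180 × 2 = 360;
- service users 60 × 3 = 180;
- family members 60 × 3 = 180;
- total 216 + 360 + 180 + 180 = 936, or 576 without community health workers.

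| Denominator | Missing | Against the limit of under 20% |
|---|---|---|
| Primary care workers only | 72/216 = 33.3% | fails |
| All groups except community health workers | 72/576 = 12.5% | passes |
| All groups | 72/936 = 7.7% | passes |

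The answer turns on a denominator that the protocol does not give. The criterion is also about collected data, so it would not register missed supervision.

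**6. Community health workers.** Table 4 schedules no questionnaire for them after training. No 8-month assessment exists for them to complete, so the final-assessment definition that suits primary care workers cannot simply be carried over.

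**The case against.** The best defence is that the progression list is shorthand for Table 1. The in-post count is the first item in the Table 1 cell, and a reader with both in hand would see that completion is also to be recorded. That may well be the intention, but the list is the place named for the scale-up decision, and its wording leaves the completion counts out.

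Second, staying in post is a legitimate feasibility question. Study design names retirement and relocation as threats and gives them as a reason for having several workers and facilities per cluster. This stands. It is a reason to report in-post status, and for community health workers it may be a reasonable retention measure, since no later questionnaire is due from them.

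Third, Discussion says that problems with retention or data collection will lead to modification, possibly with an internal pilot, so the list is not an automatic gate. This also stands and limits the consequence.

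A reader might infer two stronger conclusions. One is that the trial could be declared feasible with no usable follow-up data on workers. The documents do not support that. Table 1 would show the shortfall, and the missing-data criterion would catch it if applied within primary care workers. Some worker outcomes also do not need the worker to complete anything: diagnosis counts come from facility records, and diagnostic accuracy from interviews by a psychiatric clinical officer. The other is that the 60% is pooled and so would conceal heavy loss in one arm. The protocol does not say that it is pooled, and Data analysis reports categorical outcomes by arm and overall, so such a split would be visible.

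**Conclusion.** The finding is an inconsistency in a stated decision criterion. The same 60% at 8 months rests on employment in one place and on a set that includes completion in the other. In the test case the two give 72/72 and 0/72, on either natural reading of Table 1. The missing-data criterion does not settle the matter: 33.3% within primary care workers fails it, while 7.7% or 12.5% pooled over groups passes.

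The conflict in wording needs no assumption. The missingness figures rest on counting each planned assessment once and on every other assessment being complete. The documents give no expected turnover or completion rate, so how likely the two definitions are to disagree in practice cannot be stated. The point is worth correcting before the criterion is applied, but it does not undermine the design.

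**What to change.** Use one definition of worker retention in the progression list and in Table 1.

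- **Primary care workers:** apply the 60% to those who complete training and the outcome assessment at the final supervision session, out of all enrolled (72 planned, so at least 44). Table 4 does not tie that session explicitly to 8 months, so name the session rather than the month, or state how the two relate.
- **Community health workers:** apply the 60% to attendance at supervision during follow-up, or keep in-post status, and say the same in both places.
- **Reporting:** give in-post status as a separate figure, and show all retention figures by arm as well as overall. A pass mark in each arm is not needed.

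The cost is small. Table 1 already lists the in-post, training, supervision and outcome-measure counts, so the change is mainly one of wording. The downside is that the retention figure may come out somewhat less favourable than one based on staying in post.
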